### Quality assessment

The trial is part of the Nursing Research Network "Mitte-Süd". A report system is established within the network. Quarterly and annual quality reports have to be prepared. These reports undergo peer review and further funding is contingent on a positive review.

### Ethical considerations

The study protocol has been submitted to and approved by the ethical committee of the University Hospital Marburg.

The study relates to a research question that is still unresolved in the literature (equipoise; i.e. it is uncertain whether the intervention or the control group will benefit) and the most rigorous method to settle this issue is the randomized controlled clinical trial. According to the experience in previous trial, participating in a study like this is unlikely to be burdensome for patients [18,4,35,36]. Patients will be fully informed about the purpose of the trial and informed consent is required. All study data is kept locked and anonymous i.e. stored and evaluated using encrypted numbers. The allocation of the patients is documented in a separate reference list that is accessible only to the implementing study personnel.

## Discussion

A measurable, clinically relevant difference in the reduction of anxiety through a preoperative ICU-related information program is expected. Beyond that, interindividual differences in emotional and cognitive preoccupation will be considered that might moderate the impact of information programs and will allow to select patients that may profit most.

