**Methods/Design:**

The trial is designed as a prospective randomized controlled trial including an intervention and a control group. The control group receives the standard preparation currently conducted by surgeons and anesthetists. The intervention group additionally receives a standardized information program with specific procedural, sensory and coping information about the ICU.

A measurable clinical relevant difference regarding anxiety will be expected after discharge from ICU. Power calculation (α = 0.05; β = 0.20; Δ = 8.50 score points) resulted in a required sample size of N = 120 cardiac surgical patients (n = 60 vs. n = 60). Furthermore, N = 20 abdominal or thoracic surgical patients will be recruited (n = 10 vs. n = 10) to gain insight to a possible generalization to other patient groups.

Additionally the moderating effect of specific patient attributes (need for cognition, high trait anxiety) will be investigated to identify certain patient groups which benefit most.

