### Sample size calculation

Sample size calculation was performed with regard to the anxiety-specific part of the CINT questionnaire as the primary outcome. This score ranges between 0 and 100 with a standard deviation of SD = 17 [36]. Setting alpha at 0.05, beta at 0.20 and Δ = 8.50 (half a standard deviation as a clinically minimal relevant difference [56]) results in a required N = 100 (n = 50 patients in each group) [57]. In order to compensate for possible drop-outs that definitive number of patients to be included into this trial will be set at N = 120. This number relates to patients of the Department of Heart Surgery, a relatively homogenous group of patients.

In order to generalize findings over a wider group of patients, an additional N = 20 from the Department of Visceral, Thoracic and Vascular Surgery will be recruited.

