### Data analysis

First of all the whole trial data will be analyzed using descriptive methods: mean, median, standard deviation, frequencies including graphical presentation. Statistical testing will be focused on the cardiac surgery group (n = 120; 60 vs. 60). The main hypothesis representing the primary outcome will be tested with a two-sided t-test for independent samples assuming; the level of statistical significance is set at alpha 0.05 (two-tailed). Secondary outcomes will be tested accordingly.

An important internal analysis will be the correlation of certain individual characteristics to measure which patients benefit more from the information program than others. Especially "need for cognition" and "APAIS" measured at baseline are expected to moderate the impact of the intervention program. This will be analyzed by comparing means of subgroups using the t-test and regression modeling. This is a new study question never investigated in research on preoperative information programs.

Statistical analyses will be performed on an intention to treat basis and will be supplemented using a per protocol approach. The smaller group of patients from the Department of Visceral, Thoracic and Vascular Surgery will be analyzed using descriptive statistics and the main purpose will be to see whether the distribution of crucial outcome parameters resembles the pattern of data found in the cardiac surgery patients.

All analyses will be performed using the SPSS for Windows software.

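### The plan says the trial will allow selection of the patients who profit most, but 100 to 120 patients give adequate power only for very strong moderation

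*Protocol article*

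**What the plan says.** Two places in the protocol article promise a result about which patients benefit. The abstract (Methods/Design) says that the moderating effect of patient attributes will be studied "to identify certain patient groups which benefit most". The Discussion says that differences between individuals "might moderate the impact of information programs and will allow to select patients that may profit most". The Data analysis section presents this as an important analysis, expects need for cognition and the APAIS score to act as moderators, and plans to compare subgroup means by t-test and to use regression modelling. It names no arm-by-moderator term and no cut-point.

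The only size calculation is for the overall comparison: "This score ranges between 0 and 100 with a standard deviation of SD = 17", and "Setting alpha at 0.05, beta at 0.20 and Δ = 8.50 (half a standard deviation as a clinically minimal relevant difference", which "results in a required N = 100 (n = 50 patients in each group". For drop-outs, "patients to be included into this trial will be set at N = 120". Testing is confined to these patients: "Statistical testing will be focused on the cardiac surgery group (n = 120; 60 vs. 60".

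No section calls the moderator analysis exploratory or says how precise it can be.

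**The concern.** A trial sized for an overall difference has much less information about how that difference varies between patients. The effect difference between two halves has twice the standard error of the overall effect. The plan nevertheless presents patient selection as something the trial will deliver. This limit comes from the SD and the number of patients, so it remains even if moderation is tested correctly.

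Two misreadings are at stake. A real but moderate difference in benefit would probably not reach significance, and the result could be taken to show that all patients benefit alike. If such a difference did reach significance, its estimate would be too large. Because the plan describes this as a question not studied before in its field, readers may lean on the answer.

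**Working it through.** **Inputs** (Sample size calculation and Data analysis sections): SD 17; planned difference 8.5; two-sided alpha 0.05; power 80%; 1:1 allocation; N = 100 evaluable or N = 120 recruited, cardiac surgery patients only. Assumptions not in the documents: equal halves for the split, the same SD in every cell, one moderator without multiplicity correction, and a normal moderator wherever a continuous result is converted to halves.

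**1. The plan's own figure.** Per arm, n = 2 × (z_alpha + z_0.80)² × (17/8.5)² = 8 × (z_alpha + 0.842)².
- One-sided 0.05: 8 × (1.645 + 0.842)² = 49.5, so 50 per arm and N = 100, as stated.
- Two-sided 0.05: 8 × (1.960 + 0.842)² = 62.8, so 63 per arm and N = 126.

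The stated N therefore matches a one-sided calculation, whereas the Data analysis section says "the level of statistical significance is set at alpha 0.05 (two-tailed". That is a separate matter; the results below use the stated N and the planned two-sided level.

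**2. Moderator split into equal halves.** Each of the four cells holds N/4 patients, so SE of the effect difference = 17 × √(4/(N/4)) = 68/√N.
- N = 100: SE 6.80; 95% CI half-width 1.985 × 6.80 = 13.5.
- N = 120: SE 6.21; half-width 1.981 × 6.21 = 12.3.

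By the noncentral t distribution on N − 4 df, 80% power needs about 2.83 SE:
- N = 100: 19.2 points, and 19.2/8.5 = 2.3.
- N = 120: 17.5 points, and 17.5/8.5 = 2.1.

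**3. Moderator kept continuous.** SE of the change in effect per moderator SD = 2 × 17/√N = 3.40 or 3.10. The same multiplier gives 9.6 or 8.8 points per SD. For a normal moderator, the means of the upper and lower halves lie 2 × √(2/π) = 1.596 SD apart, so:
- N = 100: 9.62 × 1.596 = 15.4 points, 1.8 times 8.5.
- N = 120: 8.77 × 1.596 = 14.0 points, 1.6 times 8.5.

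**4. Power for two patterns that both average to the planned 8.5 points.**

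| Effect in the two halves | Difference | Split, N = 100 / 120 | Continuous, N = 100 / 120 |
|---|---|---|---|
| 12.75 and 4.25 | 8.5 | 24% / 27% | 34% / 40% |
| 17 and 0 | 17 | 70% / 78% | 87% / 93% |

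With a true difference of 8.5 in the split analysis, the halves are estimated in the wrong order with probability Φ(−8.5/SE) = 11% or 9%. A significant estimate must exceed 13.5 or 12.3 points, that is 1.6 or 1.4 times the truth.

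**5. Sensitivity (normal approximation).** Equal halves are the favourable split: the multiple of 8.5 is 2.05 to 2.24 (N = 120 to 100), rising to 2.23 to 2.45 for a 30/70 split. Covariate adjustment that explains 20–30% of the variance (an assumption) lowers the equal-split multiple to between 1.71 and 2.00.

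**The case against.** The strongest reply has four parts.

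- **The factor of two belongs to a dichotomised test.** The plan names no cut-point and allows regression, which can keep the score continuous. This stands. A reader might infer that any correct moderator test here detects only about twice the planned effect. The documents do not support that: with a continuous, normal moderator the multiple is 1.6 to 1.8 between halves, so the figure must be given with its scale.
- **Moderation would not always be missed.** This stands too. If the whole benefit sits in one half, power is 70–78% or 87–93%. The claim that relevant moderation would usually be missed holds only for smaller differences such as 8.5 points. Exaggeration is conditional in the same way: significant split estimates average about 1.9 to 2.1 times a true difference of 8.5, but only about 1.14 to 1.20 times a true difference of 17.
- **The wording is partly hedged and is no listed outcome.** The Discussion speaks of what might moderate and who may profit, the abstract states an aim, and the Outcomes section lists no moderator result. This softens the charge. It does not remove it, because the statement that selection will be possible carries no hedge.
- **Low power for interactions is ordinary, and details may sit in a fuller document.** Sizing on the main effect is not an error, and missing cut-points are no finding. But the point concerns what the article asserts, and no analysis plan can add precision to 120 patients.

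**Conclusion.** The point holds in a limited form. The plan asserts an ability to select patients that its sample size supports only if moderation is very strong. For 80% power, the effect must differ between equal halves by 17.5 to 19.2 points if the moderator is split, or by about 14.0 to 15.4 points if it is kept continuous (8.8 to 9.6 points per moderator SD). A difference as large as the whole planned effect would be found in only 24–27% or 34–40% of such trials. These figures rest on the assumptions listed with the inputs; unequal splits or several corrected moderators make them worse, and useful covariates improve them somewhat.

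A reader might go further and infer that no selection advice could ever come from this trial, or that the authors intend to read a null result as equal benefit. The documents support neither: strong moderation could be detected, and no section says how a null result would be interpreted. The primary analysis is unaffected.

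**What to change.** - In the abstract and the Discussion, replace the language of identifying and selecting patients with a hypothesis-generating aim.
- In the Data analysis section, replace the comparison of subgroup means by t-test with a regression on the continuous baseline score that contains an arm-by-moderator term, reported with its 95% CI.
- State the detectable difference on the scale of that analysis: about 9 to 10 points per moderator SD at 80% power.
- State that a non-significant interaction is not evidence of equal benefit.

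A blanket statement that no patient selection will be recommended is not needed.

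Cost: a less favourable stated claim and a small change to a secondary analysis. No extra patients are needed, and the primary analysis does not change.
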